#### 11.1.6 New cycle START, Visit 3 - D19 (D14-D24)

This visit will be performed as Standard of Care or at day 19 (+/-5days).

During this visit:

- The physician will proceed to a physical exam including collection of vital signs and clinical evaluation
- Blood samples (30mL) and fecal swabs will be collected (See Table 1 for analysis details)
- Evaluation of treatment tolerability, acceptability, compliance and safety
- Urine or serum pregnancy test will be performed

Nasopharyngeal (or any other validated methods: salivary test, oro-pharyngeal test or other) and fecal SARS-CoV-2 tests will be performed.

During this visit, the patient will report to the physician any adverse reaction or severe event occurred since the previous visit.

All AE and SAE must be reported in the eCRF.

#### 11.1.7 End of study, Visit 4 - D44 post-inclusion - Cycle STOP

This visit will be performed 44 days (+/-10days) after the MaaT033 treatment start.

During this visit:

- The physician will proceed to a physical exam including collection of vital signs and clinical evaluation
- Blood samples (30mL) and fecal swabs will be collected (See Table 1 for analysis details)
- Evaluation of treatment tolerability, acceptability, compliance and safety

Nasopharyngeal (or any other validated methods: salivary test, oro-pharyngeal test or other) and fecal SARS-CoV-2 tests will be performed.

During this visit, the patient will report to the physician any adverse reaction or severe event occurred since the previous visit. All AE and SAE must be reported in the eCRF.

After V4, patient will be followed like any AML or HR-MDS patient.

In total, 120mL of blood will be collected for each patient during the study.

|                                                                                   |                    |                                                                      |
|-----------------------------------------------------------------------------------|--------------------|----------------------------------------------------------------------|
| [figure not shown] | DOCUMENT    | Protocol ID : MPOH05
EudraCT N° : 2019-004253-89
Version: 10.0 |
|                                                                                   | CIMON STUDY | Date : 04 MAY 2021
Page 38 / 70                                   |

## **11.2 ASSESSMENTS REQUESTED FOR THE STUDY**

See Table 1 for calendar of study assessment.

- **Demographics:** gender, date of birth, birth delivery, smoking habits
- **Underlying hematologic malignancy history and assessment:** primary diagnostic date, previous treatments
- **Medical history:** Major past diseases, in the opinion of the investigator. Particular attention will be given to gastrointestinal diseases (Crohn's disease, ulcerative colitis, inflammatory bowel disease, colorectal cancer...)
- **Concomitant diseases and medications:** Chronic diseases and long-term treatments must be recorded. Record if medication is continuing during the treatment in the study.
- **Physical exam:** height, weight, vital signs: temperature, blood pressure, heart rate
- **Evaluation of MaaT033 compliance by the patient** with a diary.
- **Evaluation of induction chemotherapy response at inclusion and throughout the study**
- **Collection of AEs and SAEs (from the date of informed consent)**

|                                                                                   |                    |                                                                      |
|-----------------------------------------------------------------------------------|--------------------|----------------------------------------------------------------------|
| [figure not shown] | DOCUMENT    | Protocol ID : MPOH05
EudraCT N° : 2019-004253-89
Version: 10.0 |
|                                                                                   | CIMON STUDY | Date : 04 MAY 2021
Page 39 / 70                                   |

### **11.3 BIOLOGICAL ANALYSES REQUESTED FOR THE STUDY**

#### **11.3.1 Blood analysis**

**Table 2: List of blood assessments**

| Hematology            | Clinical Chemistry           | Immunology/markers                                     |
|------------------------------|-------------------------------------|---------------------------------------------------------------|
| Red blood cell (RBC) count   | hs-CRP                              | Multiparameter assay on plasma                                |
| White blood cell (WBC) count | Ferritin                            | Reg3α                                                         |
| Neutrophils                  | Uric acid                           | ST2                                                           |
| Lymphocytes                  | Urea                                | Immunomonitoring on Peripheral Blood Mononuclear Cells (PBMC) |
| Monocytes                    | Albumin                             | metagenomic on PBMC                                           |
| Eosinophils                  | Pre-albumin                         |                                                               |
| Basophils                    | Total protein                       |                                                               |
| Platelet count               | Triglycerids                        |                                                               |
| Hemoglobin                   | Lactate dehydrogenase (LDH)         |                                                               |
| Hematocrit                   | Cholesterol                         |                                                               |
|                              | Total and direct bilirubin          |                                                               |
|                              | Alanine transaminase (ALT)          |                                                               |
|                              | Aspartate transaminase (AST)        |                                                               |
|                              | Gamma Glutamyl Transpeptidase (GGT) |                                                               |
|                              | Alkaline phosphatase                |                                                               |
|                              | Serum Glucose                       |                                                               |
|                              | Hb1Ac                               |                                                               |

Blood hematology and clinical chemistry analyses will be performed by local hospital laboratories.

Blood collection for PBMC extraction and subsequent storage until analysis at the end of the study, will be performed by local laboratories able to perform this procedure.

Results from blood samples and feces cultures performed during patient's care will be collected in the eCRF. All lab results must be documented in the eCRF before the end of study. Additionally, reference ranges must be provided to the Sponsor or its designee.

|                                                                                   |                    |                                                                      |
|-----------------------------------------------------------------------------------|--------------------|----------------------------------------------------------------------|
| [figure not shown] | DOCUMENT    | Protocol ID : MPOH05
EudraCT N° : 2019-004253-89
Version: 10.0 |
|                                                                                   | CIMON STUDY | Date : 04 MAY 2021
Page 40 / 70                                   |

### 11.3.2 Feces analysis

**Table 3: List of feces assessments**

| Feces microbiota analysis           | Feces biochemistry      |
|--------------------------------------------|--------------------------------|
| Bacterial DNA sequencing
(metagenomics) | Neopterin                      |
|                                            | Zonulin                        |
|                                            | IgA                            |
|                                            | Biliary acids                  |
|                                            | Short Chain Fatty Acids (SCFA) |

Feces analysis will be performed in a selected central laboratory.

### 11.3.3 Management of samples

**Table 4: Samples Management**

|                                        | Blood immunology                                                          | Feces                                  | Fecal swabs                            |
|----------------------------------------|----------------------------------------------------------------------------------|-----------------------------------------------|-----------------------------------------------|
| Sample size                     | 30 mL                                                                            | at least 10g / 20mL                           | 2 swabs                                       |
| Material                        | PBMC: 2x9ml Heparin tube
Plasma: 2x6ml EDTA tube                              | Feces container
(Fecotainer®)              | Rectal swabs
(dry type)                    |
| Processing                      | Local laboratory                                                                 | Central laboratory                            | Local laboratory                              |
| Storage location and conditions | PBMC extraction within 2 to 6 hours
Storage -80°C and liquid nitrogen on site | Biochemistry:
storage -80°C until analysis | Metagenomics:
storage -80°C until analysis |
| Analysis
(end of study)     | In dedicated laboratory                                                          | In dedicated laboratory                       | In dedicated laboratory                       |

## 11.4 TERMINATION

### 11.4.1 Patient study withdrawal

Patients may be discontinued from the study in following situations:

1. Informed consent withdrawal by the patient or by the patient's legal representative;
2. Investigator's decision according but not exclusive to the following criteria:
  - Retroactive failure to fulfil inclusion/exclusion criteria;
  - Loss of contact, relocation. For lost to follow-up patients, investigator must make all possible attempts to reach the patient (phone calls, letters) with documented evidence.
  - New medical conditions not allowing for continuation of the protocol-conform treatment;

|                                                                                   |                    |                                                                      |
|-----------------------------------------------------------------------------------|--------------------|----------------------------------------------------------------------|
| [figure not shown] | DOCUMENT    | Protocol ID : MPOH05
EudraCT N° : 2019-004253-89
Version: 10.0 |
|                                                                                   | CIMON STUDY | Date : 04 MAY 2021
Page 41 / 70                                   |

- Occurrence of adverse events (such as allergic reactions to study drug, pregnancy, laboratory abnormalities) leading to substantial changes in the individual risk-benefit considerations that suggest a discontinuation of study drug
- 3. Any adverse event leading to interruption or contraindication of the MaaT033 treatment. Patients who stop treatment due to AE related to the procedure will continue to be monitored for safety follow-up. The reason for procedure stop must be documented (e.g., parenteral nutrition, impossibility to swallow).
- 4. Severe noncompliance to the protocol as judged by the investigator and/or MaaT Pharma.

In case of patient's withdrawal from the study, irrespective of the reason, an early study termination visit must be performed and recorded by the investigator in the appropriate forms of the eCRF and in the subject's medical records when considered as confirmed (e.g., date of and reason for withdrawal).

Subjects who have been withdrawn from the study cannot be re-included in the study.

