### **8.3 ENDPOINTS AND EVALUATIONS**

The studied procedure will be considered as safe if:

No severe SAE related to treatment procedure has been documented.

All patients' case profiles will be reviewed by a committee composed by 3 physicians. The main task of this committee will be to evaluate collected data and to give an opinion on treatment safety. The committee will analyze all treatment emergent AE(s) and propose categorization as treatment-related or not. In case of disagreement, majority (2 out of 3) committee's opinion will be considered as final decision.

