### 9.3 **NUMBER OF SUBJECTS PLANNED - REPLACEMENT POLICY**

The enrollment into the study will continue until a maximum of 27 subjects are treated with MaaT033 and evaluable, based on the step-up and safety process.

|                                                                                   |                    |                                                                      |
|-----------------------------------------------------------------------------------|--------------------|----------------------------------------------------------------------|
| [figure not shown] | DOCUMENT    | Protocol ID : MPOH05
EudraCT N° : 2019-004253-89
Version: 10.0 |
|                                                                                   | CIMON STUDY | Date : 04 MAY 2021
Page 27 / 70                                   |

If the compliance is under 60% for a patient, the patient will not be included in the evaluation of the dose-corresponding regimen but will be replaced by another patient.

If a patient becomes positive to SARS-CoV-2 (either nasopharyngeal, oropharyngeal swabs or salivary or other tests or feces tests) during the treatment period, it will be at the investigator's judgment to decide if the patient continues to take the capsules and stay in the study.

In case of COVID-19 pandemic in certain area of the country, an ongoing patient with unmonitored data can be considered to be replaced by another patient in another site in order to validate the corresponding dose regimen by the DSMB.

|                                                                                   |                    |                                                                      |
|-----------------------------------------------------------------------------------|--------------------|----------------------------------------------------------------------|
| [figure not shown] | DOCUMENT    | Protocol ID : MPOH05
EudraCT N° : 2019-004253-89
Version: 10.0 |
|                                                                                   | CIMON STUDY | Date : 04 MAY 2021
Page 28 / 70                                   |

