#### 11.4.2 End of study treatment

Patients would stop treatments before the end (day 7 or 14) for the following reasons:

- Life-threatening SAE related to MaaT033
- Medical decision: for instance, disease progression due to treatment failure according to the investigator's judgement

Patients who stop treatments from the study for clinical / symptomatic deterioration or disease progression will continue to be monitored for safety follow-up, survival and disease until day 44. The reason for and the date of end of treatment must be documented.

If the treatment discontinuation is related to an AE, the subject will be followed up to recovery or stabilization of the AE, whichever comes last. All definitive treatment discontinuation should be recorded by the Investigator in the appropriate pages when considered as confirmed.

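### Sections 11.4.1 and 11.4.2/12.1.3.9 conflict on what follows an AE-driven capsule stop, and none secures observation for new events up to V3, where the DLT window ends

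*Protocol*

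**What the plan says.** Section 11.4.1 of the protocol lists situations in which a patient may be discontinued from the study. The third is "Any adverse event leading to interruption or contraindication of the MaaT033 treatment". The entry continues: "Patients who stop treatment due to AE related to the procedure will continue to be monitored for safety follow-up". It gives no end date for that monitoring. For any withdrawal, whatever the reason, "an early study termination visit must be performed and recorded by the investigator".

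Section 11.4.2 deals with stopping treatment early. Patients who stop "for clinical / symptomatic deterioration or disease progression will continue to be monitored for safety follow-up, survival and disease until day 44". For AE-driven stops the rule differs: "If the treatment discontinuation is related to an AE, the subject will be followed up to recovery or stabilization of the AE". That sentence does not require the AE to be related to MaaT033, and it does not mention V3.

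Section 9.3 joins capsules and participation in one decision for a patient who becomes SARS-CoV-2 positive: "it will be at the investigator's judgment to decide if the patient continues to take the capsules and stay in the study".

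On the endpoint, sections 8.3.1 and 12.1.4.1 count DLTs from V1 to V3 (D19 ± 5 days). Relatedness is part of the DLT definition, and the committee settles it: "The committee will analyze all treatment emergent AE(s) and propose categorization as treatment-related or not". Under 8.2.2 its planned review of cohorts 2 to 5 follows completion of V3 by all six patients, and a cohort passes with no more than one patient with a DLT.

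**The concern.** Section 11.4.1 does not separate stopping capsules from leaving the study, and it makes continued monitoring depend on relatedness. At that point the only attribution available is normally the investigator's, because the committee's planned review comes after V3. A provisional judgement can therefore decide whether a dosed patient is observed to the end of the window in which the primary endpoint is counted.

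This matters when the AE that stopped the capsules is not itself ruled a DLT. A later DLT in that patient, before V3, could then go unseen, and each escalation decision rests on only six patients. A site reading 11.4.1 and a site reading 11.4.2 could follow similar patients for different lengths of time.

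**Working it through.** **Plan's own figure.** Section 9.3 gives a maximum of 27 treated and evaluable patients. Cohorts of 3, 6, 6, 6 and 6 give 3 + 4 × 6 = 27, so the figure reproduces. The concern itself rests on no stated figure.

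**The sections side by side, for a patient whose capsules are stopped for an AE that the investigator calls unrelated.**

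- 11.4.1: may be withdrawn from the study; early termination visit; no continued monitoring promised.
- 11.4.2: a treatment stop; followed until that AE recovers or stabilises. If the stop is classed as deterioration or progression, followed to day 44, which is past V3.
- 12.1.3.9: the outcome of any AE is followed, whatever its attribution.
- 12.1.3.1: all AEs from V1 to V4 are recorded regardless of relationship, but nothing says that the visits continue after withdrawal.
- None of these commits to looking for new events from resolution of the stopping AE until V3.

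**Who escapes replacement.** Section 9.3 replaces a patient whose compliance is under 60%. In whole days:

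- 7-day cohorts: 4/7 = 57% is replaced; 5/7 = 71% is not.
- Cohort 4: 8/14 = 57% is replaced; 9/14 = 64% is not.

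A 7-day patient who stops after D5 has 19 − 5 = 14 of the 19 − 1 = 18 days to nominal V3 still to run. In cohort 4, after D9, it is 19 − 9 = 10 of 18. These are the days at risk of going unobserved. They are not necessarily lost, because the stopping AE may be followed for part of them.

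**Effect on the rule.** Let p be the true probability of a DLT between V1 and V3, the same and independent across patients, and m the number of patients fully observed.

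P(pass) = (1 − p)^m + m·p·(1 − p)^(m−1)

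At p = 0.3:

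- m = 6: 0.7^6 + 6 × 0.3 × 0.7^5 = 0.1176 + 0.3025 = 0.420
- m = 5, the sixth patient counted as DLT-free with every DLT missed: 0.1681 + 0.3602 = 0.528
- Half of the sixth patient's DLTs still captured (probability 0.15): 0.1681 + 0.3602 × 0.85 = 0.474

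The protocol gives neither a DLT rate nor a withdrawal rate, so p is an assumption, shown over a range:

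| Assumed p | All six observed | One window half captured | One window fully missed | Largest rise |
|---|---|---|---|---|
| 0.2 | 0.655 | 0.696 | 0.737 | 0.082 |
| 0.3 | 0.420 | 0.474 | 0.528 | 0.108 |
| 0.4 | 0.233 | 0.285 | 0.337 | 0.104 |
| 0.5 | 0.109 | 0.148 | 0.188 | 0.079 |

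**The case against.** The strongest reply is that the rest of the protocol repairs most of what 11.4.1 leaves open, and much of that reply stands.

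- A reader might infer that follow-up is given only when the AE is called related. The protocol as a whole does not support this. Section 11.4.2 follows an AE-driven stop with no relatedness condition, 12.1.3.9 follows any AE, and 12.1.3.1 records AEs regardless of relationship.
- A reader might infer that an AE called unrelated is hidden from the committee. It is not. The committee reviews all treatment-emergent AEs and is the referee on imputability (12.1.4), so it can still rule the stopping AE a DLT. Only a new, later event can be missed.
- A reader might infer that the withdrawn patient will be counted as DLT-free. The protocol does not say so. Section 8.2.2 expects six patients to complete V3, 9.3 speaks of evaluable patients, and 12.1.4.2 lets the committee enrol more to reach the required number evaluable for DLT. That power is optional, however, and nothing states how a patient without a full window is counted.
- Withdrawal under 11.4.1 is permitted, not required, and ad hoc committee meetings are possible. Stops classed as deterioration are followed past V3.
- For SARS-CoV-2, 12.1.2 makes every COVID-19 infection an SAE, and 12.1.3.2 requires SAEs to be followed to outcome. That follows the infection. It does not secure observation for other events to V3.
- The fully-missed column is a ceiling. The example patient has taken five days of capsules, has had the D2 call, attends a termination visit and has the stopping AE followed.

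**Conclusion.** The point holds as a conflict between sections with a limited consequence for the primary endpoint. Sections 11.4.1 and 11.4.2/12.1.3.9 prescribe different follow-up for the same situation and must be reconciled. The AE that stopped treatment is secured; observation for new events from that point to V3 is not. Neither the 60% replacement trigger nor the optional enrolment in 12.1.4.2 reliably closes the gap, and 8.2.2 has no counting rule for an incomplete window.

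One fully missed window raises the chance that a six-patient cohort passes by at most about 8 to 11 percentage points over assumed true DLT rates of 0.2 to 0.5. If half of that patient's DLTs are still captured, the rise is about 4 to 5 points. The size rests on three assumptions: the rates themselves, independence with a common rate, and the incomplete patient being counted as DLT-free. It would be wrong to read 0.528 against 0.420 as the expected effect, since it is the ceiling at one assumed rate.

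**What to change.** Reconcile 9.3, 11.4.1, 11.4.2 and 12.1.3.9 so that they distinguish stopping capsules from leaving the study. When capsules are stopped remains the investigator's clinical decision, and nothing is proposed on it here. Then:

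1. State that AE/SAE collection for every patient who took at least one capsule continues at the existing V3 and V4 visits, independently of the investigator's attribution, subject to consent and contact.
2. Where observation ends before V3, record the date, so that the committee can see the incomplete DLT window.
3. State in 8.2.2 that a patient with no DLT and no complete V1–V3 window is not counted as DLT-free among the six.

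The cost is amendment wording and a few retained visits for patients already in haematology care. Table 1 already contains the visits. The counting rule may also call for an occasional additional patient, which 12.1.4.2 already allows.
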